### Data Collection and Follow-up for Withdrawn Subjects

We will use data and urine/blood samples which have already been collected for study analysis providing the patient gives consent for this to happen. Patients will have the opportunity and choice to inform the trial team how their health has been over the study duration even if they withdraw.

# Study Drug

## Description

Ergocalciferol capsules and matching placebo capsules will be provided by Mawdsley Brooks (UK). Ergocalciferol capsules will contain 50,000 International Unit (IU) (1,25mg) of ergocalciferol. The ergocalciferol capsule will be over-encapsulated into a size 00, red, empty gelatine capsule measuring 20mm and containing no markings. The placebo capsule will physically match the over-encapsulated ergocalciferol exactly.

Ergocalciferol is a white, colourless crystal, insoluble in water, soluble in organic solvents and slightly soluble in vegetable oil. One unit of vitamin D_2_ is equivalent to one IU, and 1 mcg of vitamin D_2_ is equal to 40IU.

Ergocalciferol, also called vitamin D_2_ is 9,10-secoergosta-5,7,10 (19), 22tetraen-3-ol, (3ß,5Z,7E,22E)-: (C_28_H_44_O) with a molecular weight of 396.65.

It has the following molecular composition:

[figure not shown]

## Clinical pharmacology:

The in vivo synthesis of the major biologically active metabolites of vitamin D occurs in 2 steps. The first hydroxylation takes place in the liver (to 25-hydroxyvitamin D) and the second in the kidneys (1,25 hydroxy vitamin D). Vitamin D metabolites promote the active absorption of calcium and phosphorus from the small intestine, thus elevating the serum calcium and phosphate level sufficiently to permit bone mineralization. Vitamin D metabolites also mobilize calcium and phosphate from bone and probably increase the reabsorption of calcium and perhaps also phosphate from the renal tubules.

There is a lag of 10-24 hours between the administration of vitamin D and the initiation of its action in the body due to the necessity of synthesis of the active metabolites in the liver and kidneys. Parathyroid metabolism is responsible for the regulation of this metabolism in the kidneys.

Indications:

Hypoparathyroidism, refractory rickets, familial hypophosphataemia, vitamin D deficiency

Contraindications:

Hypercalcaemia, malabsorption syndrome, hypervitaminosis D, abnormal sensitivity to the toxic effects of vitamin D

Drug interactions:

Mineral oil interferes with the absorption of fat-soluble vitamins, including vitamin D preparations.

Administration of thiazide diuretics to hypoparathyroid patients who are concurrently being treated with ergocalciferol may cause hypercalcaemia.

Carcinogenesis, mutagenesis and impairment of fertility:

No long term animal data is available

Pregnancy:

Animal studies have shown fetal abnormalities in several species associated with hypervitaminosis D which result in similar findings of supravalvular aortic stenosis described by Black in 1963.

For the protection of the fetus, the use of vitamin D in excess of the daily recommended amount during normal pregnancy should be avoided unless in the judgement of the physician, the potential benefits outweigh the risks.

Nursing mothers:

Caution should be exercised when ergocalciferol is administered to a nursing mother as there is one report of hypercalcaemia in an infant

Adverse events are generally associated with excessive intake of ergocalciferol leading to the development of hypercalcaemia. The symptoms of hypercalcaemia can include; anorexia, nausea, vomiting, diarrhoea, loss of weight, headache, polyuria, thirst, vertigo, constipation, fatigue, bone pain, muscle weakness, abdominal pain, mental disturbances, impaired renal function, kidney stones and cardiac arrhythmias.

A single, acute overdose is virtually non-toxic and requires supportive treatment with liberal fluids only. Treatment of chronic overdose with resulting hypercalcaemia consists of immediate withdrawal of the vitamin, a low calcium diet, and generous fluid intake. Severe cases may require hydration with intravenous saline together with symptomatic and supportive treatment as indicated by the patient's clinical condition. Plasma calcium and U&E's should be monitored.

## Product Sourcing Manufacture and Supply

The study drug and placebo will be sourced and supplied by Mawdsley Brooks UK. Manufacture of ergocalciferol is by Sanofi-Aventis Pharmaceuticals, [name]. Sanofi Aventis hold the Marketing Authorisation and necessary licence for product use. Mawdsley Brooks UK are supplied with ergocalciferol from the manufacturer by Pharmaceuticals Trade Services inc, [name]. Manufacture of the placebo is by

Ipswich Hospital NHS Trust Pharmacy Manufacturing Unit, [name].

## Treatment Regimen

The replacement regimen is based on current guidelines for vitamin D replacement in CKD (33)

After randomization at visit 3, patients will take 1 capsule of study drug (either placebo or active ergocalciferol) weekly for four weeks and then monthly for the following 5 months (9 doses in total).

Study visit 3: After randomization, 9 capsules of study medication will be dispensed at this visit and the patient will be observed swallowing the first dose of medication. . Patients will be told to bring back the study medicine at the next and all subsequent visits.

Study visit 4: the number of capsules remaining will be counted and the patient will be observed swallowing the medication.

Study visit 5: the number of capsules remaining will be counted and the patient will be observed swallowing the medication.

Study visit 6: the number of capsules remaining will be counted and the patient will be observed swallowing the medication.

Study visit 7: the number of capsules remaining will be counted and the patient will be observed swallowing the medication.

Study visit 8: the number of capsules remaining will be counted and the patient will be observed swallowing the medication. This will be the last dose of study medication.

Study visit 9 (last visit): no medication will be taken.

No further study drug will be dispensed after visit 3 unless the patient has lost or mislaid the medication and has an insufficient supply to complete the trial

## Method for Assigning Subjects to Treatment Groups

Subjects will be randomised to either ergocalciferol or placebo in a 1:1 fashion using a random number generator.

## Preparation and Administration of Study Drug

All study medication will be prepared and logged in the Royal London Pharmacy department. Medication will be dispensed by trained pharmacy personnel or an investigator. Subjects will be observed swallowing the medication at visits 3, 4, 5, 6, 7 and 8 by either pharmacy staff or an investigator.

## Subject Compliance Monitoring

During the first month of the trial, patients will receive nine capsules of study drug. These will be provided in a sealed container which will be checked at subsequent study visits to ensure compliance. This will avoid over frequent visits to the trial clinic and will maximize compliance. At subsequent study visits, which require attendance at the hospital, patients will be observed swallowing their medication to ensure compliance. To enhance compliance, a text message will be sent to patients if they have a mobile phone (and if they have indicated they are happy to receive a message from the study team) on the day they are due to take the study medication. The message will read “Dear NAME this is a reminder to take your vitamin D study medication today. Thank you”

## Prior and Concomitant Therapies

Prior therapies:

There will be a washout period of 2 weeks for all vitamin D therapies currently being taken by participants. The most commonly prescribed oral vitamin D analogues all have a half life of less than 14 days (Alfacalcidol— 3 hours, Calcitriol—3 to 6 hours, Ergocalciferol—19 to 48 hours) (34). Participants will be screened for use of all over the counter medicines which may contain vitamin D. It is very unlikely patients will suffer any side effects from stopping these medications for this period. Patients will be reassured about the safety of drug withdrawal and the safety and validity of undertaking a randomized, placebo controlled trial. Given that routine supplementation with vitamin D in early CKD is not routine, we anticipate that very few individuals will actually need to stop vitamin D analogues.

The patient’s general practitioner will be contacted to ensure no medicines that may contain vitamin D are being taken by participants without their prior knowledge and that no depot vitamin D preparations have been dispensed in the last 6 months.

Concomitant therapies:

Blood pressure medication should be unchanged for study period but additional therapies can be added at the discretion of the investigators if blood pressure requires clinical intervention on safety grounds. General practitioners will be asked to maintain BP medications at a stable dose. Any changes in medication by the study team will be communicated to GP’s in writing and included in the CRF. Patients will be asked to take any concomitant therapies which can affect microvascular function after clinic visits at which these assessments are made (visits 2,3,4,6,9)

Drugs which are likely to have these particular effects include aspirin and vasodilating anti-hypertensives such as calcium channel blockers. There is no evidence to suggest that iontophoresis of acetylcholine (Ach) and sodium nitroprusside (SNip) is directly affected by the presence of any antihypertensive drugs. However, there is a theoretical chance that there may be some affect on vasodilatiation particularly by drugs with a known vasodilatory effect eg calcium channel blockers. Hence, patients will be asked to take all their daily medications after all microcirculatory assessments have been made.

Aspirin has been shown to affect microcirculatory response to AcH and SNip but this effect can be corrected by measuring skin resistance (35). However, another group has shown no effect of aspirin on the response to AcH (36). The maximum half life of aspirin is 20 hours at high doses but is as low as 6 hours when lower doses are used (34) and therefore even a dose taken the day before iontophoresis assessments is very unlikely to affect the results.

Patients will be asked at each visit if they have been prescribed or if they have bought any other medicinal or herbal product which may interfere with the study. If a new drug is being taken, a decision to withdraw the subject will be made by the Principal Investigator based on its pharmacology and pharmacokinetics. All details of concomitant medications will be recorded in the Case Report Form (CRF).

There are no dietary restrictions or restrictions on the use of tobacco or alcohol during this study but patients will be asked to refrain from smoking for 4 hours before undergoing microcirculatory assessments.

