## Primary Study Endpoints

**1. Microcirculatory studies** – pulse wave velocity (PWV), iontophoresis of acetyl choline (AcH) and sodium nitroprusside (SNip), skin autofluoresence (AF) and side stream dark field imaging of the sub lingual microcirculation.

Pulse wave velocity – we expect PWV to decrease after vitamin D therapy.

Iontophoresis – we expect lower skin micro-vessel resistance as measured by laser Doppler Flowmetry (LDF) after vitamin D therapy.

Skin autofluorescence – we expect lower deposition of advanced glycation end products after vitamin D therapy.

Sublingual microvascular flow using sidestream darkfield (SDF) imaging – we expect enhanced flow in patients treated with vitamin D

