Iontophoresis

1. This will occur immediately after skin autofluorescence under the same environmental conditions
2. Iontophoresis will be conducted and measured by a MIC 2 controller and DRT4 LDF monitor (Moor instruments, UK)
3. Iontophoresis will be assessed in response to 1% AcH and 1% SNip.
4. Forearm skin (left and right) will be gently cleaned with an alcohol based swab and any dead skin will be removed by gently placing adhesive medical tape over the affected skin areas.
5. The following doses will be administered:

| **Current (mA)** | **ACH** | **SNip** |
| --- | --- | --- |
| 0 | 60 sec | 60 sec |
| 10 | 30 sec | 30 sec |
| 0 | 60 sec | 60 sec |
| 20 | 30 sec | 30 sec |
| 0 | 60 sec | 60 sec |
| 35 | 30 sec | 30 sec |
| 0 | 60 sec | 60 sec |
| 50 | 30 sec | 30 sec |
| 0 | 60 sec | 60 sec |
| 75 | 30 sec | 30 sec |
| 0 | 60 sec | 60 sec |

Sub lingual side stream dark field microscopy

1. Several recordings of the sublingual microcirculation will be made each of 60 seconds
2. This will be conducted by a side stream dark field imager (Microvision, UK)
3. Sterile probes will be used for each patient
4. The probe is inserted under the tongue for 60 seconds on 2 occasions 1 minute apart
5. Video images will be recorded for analysis at a later date

Blood samples

1. If required by protocol, venesection will occur under sterile conditions from the dominant arm.

A single sample of 100 mls will be taken at visits 3,4,6,9. At other visits, 20 mls of blood will be taken.

3. Labelling: Tubes will be labelled with the following information

Pt initials

Pt trial number

Date

Time

Protocol number

**4. Residual Samples:** All residual samples will be destroyed following completion of planned assays.

Urine samples

1. As required by the protocol, a ~25 ml mid stream urine sample will be collected

2. Urine samples will be split into two sterile containers. One sample will be analysed at the Royal London Hospital for urine PCR and Na. Another sample will be stored for future analysis in a -80 degree Celsius fridge at the Royal London Hospital. This will be centrifuged so only the acellular component is retained.

**3. Residual Samples:** All residual samples will be destroyed following completion of planned assays.

Other clinical samples

1. Cardiac MRI: To be conducted at the London Chest Hospital

This examination is carried out by specialist doctors and nurses.

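### Skin resistance is named as the correction for aspirin's effect on the iontophoresis response but is never measured, and the treatment comparison does not adjust for aspirin use

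*Combined protocol and SAP*

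**What the plan says.** Prior and Concomitant Therapies (5.7 in the table of contents) lists aspirin among the drugs likely to affect microvascular function, then treats it in four steps:

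- Effect and correction: "Aspirin has been shown to affect microcirculatory response to AcH and SNip but this effect can be corrected by measuring skin resistance (35").
- Contrary evidence: "However, another group has shown no effect of aspirin on the response to AcH (36"). Nothing is said about SNip in that second study.
- Half-life: "The maximum half life of aspirin is 20 hours at high doses but is as low as 6 hours when lower doses are used (34"), from which it concludes "therefore even a dose taken the day before iontophoresis assessments is very unlikely to affect the results".
- Timing on visit days: "patients will be asked to take all their daily medications after all microcirculatory assessments have been made". Doses on earlier days are not restricted.

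The same section has all concomitant medication recorded in the CRF.

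Sample Size Determination powers the study on iontophoresis. Allocation is 1:1 from a random number generator, with no stratification mentioned. Statistical Methods compares means by t test. It adds multiple regression to find factors associated with better microvascular function, but names no covariates.

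**The concern.** The protocol itself says that a common drug alters the response to both iontophoresis agents, and iontophoresis is the outcome on which the sample size rests. It then offers two reassurances: a measurement that corrects the effect, and a pharmacokinetic argument that the previous day's dose is harmless. If the measurement is not taken and the argument holds only for some doses, aspirin differences between patients stay in the error term of the main comparison. A chance excess of users in one arm would then shift the estimate without any planned adjustment.

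**Working it through.** **1. The plan's own sample size.** From Sample Size Determination: [(15 × 85) + (50 × 50)] / 35² × 10.5 = 3775 / 1225 × 10.5 = 32.4, which the plan gives as 32 per arm, raised to 40 for losses (32 / 0.8 = 40). The formula reproduces the figure, and this point does not dispute it. It matters here only because it makes iontophoresis the powered endpoint.

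**2. Is skin resistance measured or used anywhere?**

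- Attachments, Iontophoresis SOP: "Iontophoresis will be conducted and measured by a MIC 2 controller and DRT4 LDF monitor (Moor instruments, UK"). The other steps give conditions, drug strength, skin preparation and a table of currents and times. There is no resistance or voltage reading.
- Study Procedures and Schedule of Assessments: a laser Doppler probe records the response. Neither the text nor the visit table includes resistance.
- Appendix 1 visit table: the same.
- Statistical Methods: no correction for resistance.
- Primary Study Endpoints: "we expect lower skin micro-vessel resistance as measured by laser Doppler Flowmetry (LDF) after vitamin D therapy". This is resistance of the micro-vessels, an expected outcome read from blood flux. It is not the skin measurement proposed as a correction.

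So the correction is named once and implemented nowhere.

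**3. The half-life argument.** Fraction of a dose left = 2^(−gap / half-life). The half-lives are the protocol's. The protocol gives no gap, so 12 to 24 hours is assumed. Twenty-four hours fits a once-daily dose taken at the same hour as the assessment, and 12 hours fits an evening dose.

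| Half-life | 12 h gap | 24 h gap |
| --- | --- | --- |
| 6 h (lower doses) | 2^(−2) = 25% | 2^(−4) = 6% |
| 20 h (stated maximum, high doses) | 2^(−0.6) = 66% | 2^(−1.2) = 44% |

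The conclusion is reasonable in the 6-hour, 24-hour cell. It does not follow at 20 hours. The fraction of drug left is only a proxy for any effect on the skin response.

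**4. Possible size in the comparison.** The documents give neither the share of aspirin users nor the size of the effect. Assumptions for illustration: prevalence p of 30-50%, an aspirin effect of d = 0.5 SD (SD among patients with the same aspirin status), and 40 per arm.

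- Variance explained = d²p(1−p) / [1 + d²p(1−p)]. At p = 0.3: 0.0525 / 1.0525 = 5.0%. At p = 0.5: 0.0625 / 1.0625 = 5.9%.
- Chance imbalance between two binomials of 40: a difference of at least 6 users in about 18-22% of trials, and of at least 8 in about 7-9%.
- Shift from a 6-user imbalance: (6 / 40) × 0.5 = 0.075 SD. The standard error of the difference is √(2/40) = 0.224 SD, so the shift is 0.075 / 0.224 = 0.34 of a standard error.
- Range over d, with the same formulas: at half the effect (0.25 SD) the shift is 0.15 × 0.25 = 0.0375 SD and the variance share is 0.0131 / 1.0131 to 0.0156 / 1.0156, or 1.3-1.5%. At double (1.0 SD) the shift is 0.15 SD and the share is 0.21 / 1.21 to 0.25 / 1.25, or 17-20%.

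These figures treat the outcome as continuous, as the t test does. They are not mapped to the 85% versus 50% failure rates used for the sample size.

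**The case against.** The strongest reply is that randomisation already protects the comparison. Baseline aspirin use is independent of arm in expectation, chance imbalance is reflected in the t test's standard error, and the unadjusted test remains valid. That stands. A reader might infer that the treatment estimate is biased, but the documents do not support that.

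A reader might also infer that the plan has no means of checking or correcting for aspirin. This is wrong: the CRF holds the medication data, and Statistical Methods provides for multiple regression. What is missing is a commitment to use aspirin as a covariate in the treatment comparison. The regression as described is a search for associated factors.

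Third, it is tempting to say that the half-life argument fails outright. It does not. The protocol presents 20 hours as a maximum at high doses, nothing says that participants take high doses, and the 6-hour figure supports the conclusion for a gap near 24 hours. Deferring visit-day doses helps, and the cited evidence on AcH is mixed.

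Fourth, the magnitude rests on assumed prevalence and effect, and is small at the central assumption: 5-6% of variance is worth about 2 patients per arm (0.05 × 40 = 2.0; 0.059 × 40 = 2.4). Microcirculatory tests at two pre-treatment visits could also absorb the effect of stable aspirin use if baseline were adjusted for, although Statistical Methods does not say that it will be.

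Finally, one might extend the point to the platelet-activity endpoint. The protocol's aspirin argument concerns iontophoresis only, and the documents give nothing with which to size such an extension, so it is not made here.

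**Conclusion.** The concern holds in a limited form. The protocol relies on a skin-resistance correction that no procedure or analysis contains, and its half-life statement is wider than its own figures allow: sound at 6 hours with a gap near 24 hours, unsound at 20 hours. The consequence is avoidable noise and uncorrected chance imbalance in the powered endpoint. The trial's validity is not in question. The loss cannot be computed from the documents. It is probably modest, at the one-third of a standard error and 5-6% of variance shown above if the 0.5 SD and 30-50% assumptions are near the truth. The case for acting is that adjustment costs almost nothing and that the protocol itself names aspirin as likely to affect this outcome.

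**What to change.** 1. **Statistical Methods.** Before unblinding, pre-specify baseline aspirin use (yes/no, from the CRF at or before the randomisation visit) as a covariate in the treatment comparison of the iontophoresis outcomes, replacing the unadjusted t test with a linear model containing treatment and aspirin. Cost: one degree of freedom (80 − 2 = 78 becomes 80 − 3 = 77 with full recruitment) and no new data.
2. **Reconcile Prior and Concomitant Therapies with the Iontophoresis SOP.** If the existing equipment already reports skin resistance, add its recording to the SOP and state how it enters the analysis. If not, stop citing it as the correction. Cost: an equipment check, then either one extra reading per current step or a text edit. Whether the equipment reports resistance is not stated, and the documents give no correction formula.
3. **Limit the half-life statement** to the lower-dose figure and a gap near 24 hours. Cost: a text edit. On its own this changes no result.

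No change to patients' aspirin use is proposed.

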## Packaging

The packaging and labelling of the IMP will be in accordance with applicable local regulatory requirements.

Study medicine kept at the pharmacy in the Royal London Hospital will be in sealed containers with appropriate clinical trial labelling. Each container will contain nine (9) capsules. Patients will receive a labelled container of nine (9) capsules to take home with them after study visit three. These will be labelled in accordance with trial protocol.

## Blinding of Study Drug

Both the investigators and patients will be blinded to the study drug. Mawdsley Brooks UK will facilitate randomisation and blinding of the study subjects. A master randomisation list will be held at Mawdsley Brooks UK with a copy kept at the Royal London Hospital Pharmacy department.

## Receiving, Storage, Dispensing and Return

### Receipt of Drug Supplies

The investigator is responsible for ensuring IMP accountability, including reconciliation of IMP and maintenance of IMP records, throughout the trial in accordance with regulatory requirements.  Upon receipt of IMP, the investigator (or Pharmacist) will check for accurate delivery and acknowledge receipt and signing (or initialling) and dating the documentation provided by the sponsor and returning it to the sponsor.  A copy will be retained for the investigator file.

